## Abstract

**Background:**

Premenstrual syndrome (PMS) is one of the most widespread menstrual disorders in women of reproductive age. This recurrent syndrome is a combination of physically, mentally, or behaviorally disturbing changes occurring during the secretory phase of the menstrual cycle. The aim of this study is to determine the effect of a cognitive-behavioral therapy-based educational intervention using social networks on PMS in female health center employees in Rudbar, Iran.

**Methods/design:**

A randomized superiority controlled trial will be conducted involving 140 female employees of health centers affiliated with the Guilan University of Medical Sciences, Rudbar. The study involves a block size of 4 and 6 in a randomly varied order, 140 women who meet all the inclusion criteria will be randomly and equally divided into 2 groups: the intervention and the control groups. Those in the former group will receive a cognitive-behavioral therapy-based treatment for eight consecutive weeks on the social network platform WhatsApp; however, those in the control group will not be offered any treatment except usual care practices (unprotocolized usual care). The study’s primary outcome is the severity of PMS symptoms, and the secondary outcomes include general self-efficacy, work-related quality of life, the impact of PMS on daily life, coping with the symptoms, and experiencing anxiety and depression at the beginning of the study to identify people with PMS. A daily record of the symptoms will be completed for two consecutive months by all female employees aged 20–45 years who wish to participate in the study. According to the initial screening, those with moderate to severe PMS will be included. We will use the MLwin software for the analyses. All questionnaires will be completed by both groups immediately and 8 weeks after the termination of the treatment. The data will be analyzed using linear mixed-effects modeling with random intercepts and slopes.

**Discussion:**

It is anticipated that the findings of the present study may demonstrate the effectiveness of the cognitive behavioral therapy intervention on the severity of PMS symptoms that could guide healthcare providers in opting for suitable treatment alternatives for the syndrome.

**Ethics and dissemination:**

The research proposal is approved by the Human Ethics Committee of Qazvin University of Medical Sciences (IR.QUMS.REC.1399.252). The results of this intervention trial will be submitted for publication in a peer-reviewed research journal.

**Trial registration:**

Iranian Registry of Clinical Trials IRCT20180218038789N4. Registered prospectively on October 28, 2020

## Introduction

Premenstrual syndrome (PMS) is one of the most common menstrual disorders in women of reproductive age [1]. This syndrome is a recurrent combination of bothersome physical, psychological, or behavioral changes during the secretory phase of the menstrual cycle [2] which decrease rapidly with the onset of menstruation [3, 4]. Its most common symptoms are anxiety, depression, fatigue, anger, irritability, feeling out of control, confusion, changes in appetite and sleep, bloating, and breast tenderness. These symptoms and their severity unquestionably vary among females, rendering its diagnosis difficult [5–7].

The high prevalence of PMS is a major concern in many settings [8]; however, due to the variety and severity of its symptoms, it is challenging to estimate its prevalence [9]. Yonkers et al. [10] and Potter et al. [11] have estimated that PMS affects 20% of women of childbearing age.

The PMS symptoms affect women’s quality of life and disrupt many aspects of it, including daily activities, interpersonal relationships, social activities, sexual function, and occupational function. Additionally, they can cause disturbances in couples’ relationships, incompatibilities with children, absence from workplaces, and social consequences such as increased accidents and abuse [12]. The surge in job conflicts as well as the growing demand for divorce by women in the premenstrual period has led to confusion and serious dangers in their lives [13, 14]. The syndrome escalates the direct costs of treatment and also the indirect expenses associated with reduced work productivity and efficiency to a significant extent [15].

Therapeutic goals for treating PMS include reducing the extent and severity of symptoms as well as their impact on personal activities and relationships and improving the quality of life [16]. Because the underlying cause of the condition is unknown, several treatments have been recommended to regulate it, including medication, non-pharmacological treatment, and surgical treatment [17]. According to the American College of Obstetricians and Gynecologists [18], the choice of treatment strategy depends on the severity of the PMS symptoms. The use of non-pharmacological methods is usually employed as the first strategy for mild to moderate cases, and drug remedies are used for those that are severe or interfere with daily functioning [19]. However, a cross-sectional study showed that only 48% of the participants with PMS sought medical treatment [20].

Pharmacological treatment of PMS includes vitex agnus-castus (only herbal medicine proven to control PMS-associated mood swings and irritability), combination oral contraceptives, and selective serotonin reuptake inhibitors (considered as the first-line treatment of PMS with predominantly emotional symptoms) [17]. Because drugs are often associated with significant side effects such as nausea, weakness, and headache, a substantial number of women discontinue their use despite the evidence of their effectiveness. Side effects, and consequently, the high rate of non-adherence as well as the desire of women to cope with the symptoms naturally, have undoubtedly limited the practicality and applicability of medications [21–23]. Concerns regarding their aftereffects have led those with PMS to request non-pharmacological interventions [24].

Non-pharmacological treatment includes lifestyle modification, dietary supplementation, and cognitive behavioral therapy [17]. Nonetheless, there is limited evidence to support the effectiveness of lifestyle modifications [25–28] and dietary supplementation [29–31] as independent forms of treatment of PMS. Although the causes of PMS are multidimensional and consist of physical, psychological, and cultural factors, current studies have mainly focused on physical interventions. Psychological interventions have been suggested as another treatment alternative for PMS symptoms; CBT is a psychological approach with the best evidence of its usefulness [32, 33].

CBT is based on the idea of how we think (cognition) and feel (emotions) and the manner in which we interact with each other (behavior). Therefore, negative and irrational thoughts can cause discomforts and problems [34]. CBT consists of limited weekly sessions focusing on correcting negative and abnormal thoughts as well as educating individuals on effective adaptive mechanisms. Its effects are achieved over time and, last, even when the sessions are completed. Conversely, drug therapy has a very rapid influence that ends with its discontinuation [35, 36]. These outcomes demonstrate the potential of CBT as a promising treatment alternative leading to long-term sustainable progress and also highlight the important role of coping strategies. However, these findings require further research [37, 38].

Due to the serious consequences and negative effects of this syndrome on the activity and performance of individuals, the very important role of women in the family and society, increasing the number of workers, and very few studies on the effects of PMS in the workplace, the target group of this study was health workers. They are one of the most important occupational groups in promoting community health and are themselves role models for different groups of people. Therefore, the present study was designed to determine the effect of a CBT-based educational intervention using social networks on PMS in female employees of health centers in Rudbar, Iran.

## Methods

### Study design

The present research is a block randomized superiority controlled trial that will be performed in the health centers affiliated with Guilan University of Medical Sciences, Rudbar, Iran. Figure 1 shows the study CONSORT flowchart.

**Fig. 1 Fig1:**
[figure not shown]
CONSORT flow diagram

### Participants

The research population in the present study includes female employees aged 20–45 years in the Rudbar health centers who will be invited to participate using the convenience sampling method.

#### Inclusion criteria

The following are the inclusion criteria:
Willingness to participate in the studyAge 20–45 yearsModerate-to-severe PMS or PMDD (based on PMS screening using a daily symptom registration form)Having internet accessPossessing a smartphone

#### Exclusion criteria

The following are the exclusion criteria:
Diagnosis of psychosis or bipolar disorder, ED, and moderate-to-severe depressionParticipated in a psychotherapy program for PMS at present or in the pastAcute suicide tendenciesChildbirth or breastfeeding during the past three monthsPregnancyGynecological diseases (hysterectomy, oophorectomy, cervical cancer, polycystic ovary syndrome, endometriosis, and infertility)Using any kind of antidepressants, benzodiazepines, antipsychotics, oral contraceptives, or hormones over the past 3 months

### Sample size estimation

The intervention effect will be evaluated by comparing the mean score of PMS symptom severity (primary outcome measure) between the two groups. Thus, the sample size was calculated based on the ability to detect a clinically relevant difference of 30% between the two groups in 8 weeks after intervention (30% reduction in the mean PMS score). This sample size accounted for a type I error rate of 0.05, any-pair power of 0.95, and all-pair power of 0.85. Based on the evidence from a previous study [39] and assuming a mean = 163.6, SD = 89.5, in group 1 and mean = 115.0, SD = 89.5, in group2 and an estimated reduction of 30% in the mean PMS score due to the intervention, the target sample size was calculated at 62 patients per group, with a 10% loss to follow-up, and to increase the power of the study, we selected 70 women in each group for a total sample size 140.

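### Two powers, 0.95 and 0.85, are stated for one two-group comparison; 62 women per group supports only 85%

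*Protocol article*

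**What the plan says.** The Sample size estimation section of the protocol article rests the calculation on "comparing the mean score of PMS symptom severity (primary outcome measure) between the two groups", and on a "clinically relevant difference of 30% between the two groups in 8 weeks after intervention". It gives a "type I error rate of 0.05" without saying whether the test is one- or two-sided, and then states two powers: "any-pair power of 0.95, and all-pair power of 0.85".

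The planning values are "mean = 163.6, SD = 89.5, in group 1 and mean = 115.0, SD = 89.5, in group2". The result is that "the target sample size was calculated at 62 patients per group, with a 10% loss to follow-up". The section then raises this to 70 per group, 140 in total, and cites higher power as a further reason for doing so.

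The abstract says that the women will be "randomly and equally divided into 2 groups". Sampling and randomization likewise has two arms only, A for intervention and B for control. The Intervention section lists a single primary outcome, the severity of PMS symptoms.

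**The concern.** Any-pair power is the probability of detecting at least one true difference among several pairwise comparisons. All-pair power is the probability of detecting every one of them. The distinction needs at least three groups, or some other set of several comparisons. With two groups there is one pair, so at least one and every one are the same event and the two powers must be equal. The section names no third arm, second contrast or co-primary outcome that would separate them.

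One of the two figures must therefore be wrong for this trial. If it is the 0.95, the article offers a 5% risk of missing the target effect that the design does not deliver. That matters most if the primary result is null, because a reader may then treat it as stronger evidence against a 30% effect than it is. As printed, the reader also cannot tell which power the trial was designed for.

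**Working it through.** **Inputs, all from Sample size estimation unless noted**

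- Means 163.6 and 115.0, common SD 89.5
- Alpha 0.05. Sidedness is not stated; two-sided is assumed first and one-sided is tried below
- Equal allocation (abstract)
- Loss to follow-up 10%
- Calculated size 62 per group, final size 70 per group

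**Effect size**

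- Difference: 163.6 − 115.0 = 48.6
- Relative reduction: 48.6 / 163.6 = 29.7%, consistent with the stated 30%
- Standardised difference: d = 48.6 / 89.5 = 0.543

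**Reproducing the 62**

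Normal approximation: n per group = 2 × (z for alpha + z for power)² / d².

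- Two-sided, power 0.85: 2 × (1.960 + 1.036)² / 0.543² = 60.9, so 61. The exact t-test (noncentral t) gives 61.9, so **62, the article's figure**.
- Two-sided, power 0.95: 2 × (1.960 + 1.645)² / 0.543² = 88.1, so 89. The t-test gives 89.1, so **90**.

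The stated 62 is the answer for power 0.85, not for 0.95.

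**Allowance for loss**

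- 62 / (1 − 0.10) = 68.9, so 69; the article rounds up to 70.
- 70 × 0.90 = 63 evaluable per group, one more than the 62 required.

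**Power at the article's sizes**

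| Evaluable per group | Two-sided, t-test | Two-sided, normal | One-sided, t-test | One-sided, normal |
|---|---|---|---|---|
| 62 (calculated) | 85.1% | 85.6% | 91.3% | 91.6% |
| 63 (70 less 10%) | 85.6% | 86.2% | 91.7% | 92.0% |
| 70 (no loss) | 89.1% | 89.5% | 94.0% | 94.2% |

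The two-sided risk of missing the effect is 100 − 85.1 = 14.9% at 62 and 100 − 85.6 = 14.4% at 63. Going from 62 to 63 evaluable women adds about half a percentage point, so once the planned loss has occurred the rounding up to 70 hardly raises the power.

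**Other readings that might rescue 0.95**

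- *One-sided test.* Power 0.95 needs 75 per group by t-test (74 normal), and power 0.85 needs only 50 (49 normal). Neither reproduces 62.
- *A reduction of exactly 30%.* The difference becomes 0.30 × 163.6 = 49.08, and two-sided power at 62 is 85.8%.
- *Baseline adjustment.* Adjustment multiplies the required n by (1 − r²), where r is the correlation between baseline and outcome. For 95% power, r = √(1 − 62/88.1) = 0.54 at 62 per group, 0.53 at 63, and 0.45 at 70 with no loss. The section assumes no such correlation.

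**Size that 0.95 would need**

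90 evaluable per group, two-sided t-test; 90 / 0.90 = 100 randomised per group.

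**The case against.** The best case for leaving this alone is that almost everything in the calculation is right. The 30% reduction, the 62 per group and the step to 70 all reproduce, and the correct power, 0.85, is printed beside the wrong one. On that view the fault is a redundant label, not an underpowered trial. This is fair as to consequence: the design needs no change. It does not make the sentence true. It assigns two values to one quantity, and the more favourable value is unsupported.

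A second objection is that 85% to 89% belongs to an unadjusted two-sided t-test, whereas the Data analysis method section plans a covariate-adjusted linear mixed model on repeated assessments that begin at baseline. Symptom severity at baseline is itself an average over two months of diaries, so the planned analysis may be more powerful. That stands as a caveat on the 14% to 15% miss rate. It does not support 0.95, because the sample size section neither states nor uses a baseline correlation.

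Third, two-sidedness is an assumption. It is, but it is the reading that reproduces 62 at one of the two stated powers. One-sided testing reproduces 62 at neither and still falls short of 95%, even with all 70 women per group retained.

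**Conclusion.** The concern holds. With two groups and one primary comparison, any-pair and all-pair power coincide, so the two stated values contradict each other. The inputs identify 0.85 as the figure behind the sample size. Power is about 85% at 62 per group, 86% after the planned loss from 70, and 89% if nobody is lost. The overstatement is about 9 to 10 percentage points at the planned number of evaluable women, and about 6 points at best.

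This rests on the stated means and SD, a two-sided alpha of 0.05, and an unadjusted two-sample t-test at one time point. The defect lies in the stated power, not in the sample size: 140 is adequate for 85% power with 10% loss.

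**What to change.** In Sample size estimation, delete the any-pair and all-pair figures and state a single power with the test and sidedness behind it. Suggested wording:

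> With a two-sided type I error of 0.05, 62 evaluable women per group give 85% power (two-sample t-test) to detect a difference between means of 163.6 and 115.0 with SD 89.5. Randomising 70 per group allows for 10% loss to follow-up, leaving 63 evaluable per group and 86% power.

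The sponsor should confirm that the two-sided test is what was intended. The statement that the increase to 70 raises power should be dropped or limited to the case of less than 10% loss.

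The cost is one rewritten sentence and a less favourable stated power. N = 140, randomisation, outcomes and analysis are unchanged, and no additional women are needed. Keeping a 0.95 claim on these inputs would instead require about 100 women per group.

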#### Symptom diary to assess the severity of PMS

The severity of premenstrual symptoms was assessed based on the severity of 27 physical, and behavioral symptoms as well as 3 items related to interference with social activities were measured using a PMS symptom diary validated by Janda et al. [40] prospectively. Therefore, the participants will be requested to complete a daily prospective record of their symptoms during two consecutive menstrual periods using a 4-point Likert scale (0 = *normal*, 1 = *low*, 2 = *moderate*, 3 = *severe*). The effects of these symptoms on social aspects are examined. According to the DSM-V criteria for severe PMDD and PMS, a minimum of 5 symptoms (including a behavioral symptom) of the 27 primary items should be present (more than 2), with at least one of them related to the impact on social aspects (greater than 2) for no less than 2 days in the luteal phase [40].

For each woman, scores related to symptom severity (SI score) and severity of the interference with social activities (INT score) will be calculated. The first 27 items are used to calculate the SI score, and items 28 to 30 are used to calculate the INT score, which indicates social and occupational interference. These scores are calculated for the luteal phase. Luteal phase scores are calculated according to the last 7 days before menstruation. Only symptoms that are rated higher than or equal to 2 for at least 2 days will be entered into the calculation. The values of all items with a score greater than or equal to 2 for at least 2 days are added together and divided by 7 [40]. Therefore, the average severity of PMS symptoms per person will be calculated.

It should be noted that the symptom record sheet should be completed 2 months before the intervention starts, in order to diagnose PMS symptoms and assess the severity of PMS; the average of these 2 months will be considered as a baseline score. The severity of PMS will be assessed for 1 month immediately and 8 weeks after the end of the intervention to evaluate the short-term and long-term effects of the intervention.

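### The planning means and SD behind the sample size cannot be values of the primary severity score as the protocol defines it, and their scale is not stated

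*Protocol article*

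**What the plan says.** Under Sample size estimation, the protocol article says the intervention effect will be evaluated by "comparing the mean score of PMS symptom severity (primary outcome measure) between the two groups". The planning values, taken from a cited previous study, are "assuming a mean = 163.6, SD = 89.5, in group 1" and "mean = 115.0, SD = 89.5, in group2", described as "an estimated reduction of 30% in the mean PMS score due to the intervention". The error rates are given as "type I error rate of 0.05, any-pair power of 0.95, and all-pair power of 0.85", and "the target sample size was calculated at 62 patients per group". This is raised to 70 per group to allow for 10% loss to follow-up and to add power.

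Under Symptom diary to assess the severity of PMS, each item is rated 0 to 3. "The first 27 items are used to calculate the SI score", while items 28 to 30 form a separate interference score. The window is the last seven days before menstruation. Values of items "with a score greater than or equal to 2 for at least 2 days are added together and divided by 7". The baseline score is the average of two months, and each follow-up assessment covers one month.

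The article does not name the instrument or scoring of the previous study, and gives no conversion to the diary score.

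**The concern.** The sample size section ties its figures to the primary outcome, and the diary section defines how that outcome is scored. The two are incompatible: both planning means lie above the highest score a woman can have. This is a stated figure that cannot be right for the stated endpoint, not a detail left to a fuller document.

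Two things depend on it. First, the clinically relevant difference has no readable meaning in endpoint units: 163.6 − 115.0 = 48.6 points would be 60% of the whole 0 to 81 range. Second, power for a relative reduction depends on the ratio of SD to mean. The borrowed ratio, 89.5/163.6 = 0.547, need not hold for the diary score, which sets to zero any item not rated 2 or more on at least two days.

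**Working it through.** **Inputs.** From Sample size estimation: means 163.6 and 115.0, SD 89.5, alpha 0.05, power 0.85 or 0.95, 62 per group, 10% loss, 70 per group selected. From the diary section: 27 severity items, 3 interference items, top rating 3, seven days, divisor 7. Sidedness is not stated; two-sided is assumed.

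**1. The plan's own figure.**
- Difference: 163.6 − 115.0 = 48.6, which is 48.6/163.6 = 29.7% of the first mean.
- Standardised difference: d = 48.6/89.5 = 0.543.
- Normal approximation: n = 2(1.960 + 1.036)²/0.543² = 60.9, so 61 per group at power 0.85. The t-test version gives 61.9, so 62. The stated figure reproduces.
- Loss to follow-up: 62/0.90 = 68.9, so 69; the plan takes 70.
- t-test power is 85.1% at 62 per group and 89.1% at 70. Power of 0.95 would need 89 (normal) or 90 (t-test) per group, so 62 matches only the 0.85 figure.

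**2. The range of the endpoint.**
- Maximum severity score: 27 × 3 × 7 / 7 = 81.
- With the interference items added: 30 × 3 × 7 / 7 = 90.
- Largest possible SD on 0 to 81: 81/2 = 40.5, reached when half the women score 0 and half score 81. On 0 to 90 it is 45.
- Averaging two baseline months leaves the maximum at 81. The threshold rule can only lower scores.

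So 163.6, 115.0 and 89.5 all fall outside what the score allows, with or without the interference items.

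**3. Assumption A: undivided seven-day sums of this diary under the same item rule.** The maximum is then 27 × 3 × 7 = 567, and all three figures fit.
- Means: 163.6/7 = 23.4 and 115.0/7 = 16.4.
- SD: 89.5/7 = 12.8. Difference: 48.6/7 = 6.9.
- d stays 0.543, and n and power are unchanged.

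**4. Assumption B: another instrument.** The documents give no mean or SD on the 0 to 81 scale, so no corrected N can be computed. For a 30% reduction, d = 0.30/(SD/mean). Two-sided unadjusted t-test power, with SD/mean assumed:

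| SD/mean | d | 62 per arm | 70 per arm |
|---|---|---|---|
| 0.45 | 0.667 | 0.96 | 0.97 |
| 0.547 (as borrowed) | 0.548 | 0.86 | 0.90 |
| 0.65 | 0.462 | 0.72 | 0.77 |
| 0.70 | 0.429 | 0.66 | 0.71 |

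The 0.547 row is slightly above the figures in step 1 because it uses exactly 30% rather than 29.7%.

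**The case against.** The strongest reply is that sample size depends only on the standardised difference. That is 0.543 whatever the units, and 62 per group follows from it. The effect is also framed as a relative reduction, which survives division by 7. If the cited study reported undivided sums of the same diary, all that is missing is a note to divide by 7. This stands: a reader might infer that 62 is miscalculated or that the trial is underpowered, and the documents support neither. Which case applies depends on a source that is not at hand, and nothing in the article favours a ratio of 0.65 or 0.70 over 0.547.

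It is also fair that the power figures under assumption B describe an unadjusted comparison at one time point, whereas the Data analysis method section plans a mixed model with repeated assessments and covariate adjustment. As an illustration, a baseline to follow-up correlation of 0.5 (assumed; not in the documents) with the efficiency of an analysis of covariance would give power of about 0.94, 0.84 and 0.78 at ratios 0.547, 0.65 and 0.70 with 62 per arm. The tabulated values are therefore not the power of the planned analysis. They show how far the planning claim moves with the ratio.

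The reply does not remove the mismatch. The article prints both the planning values and the scoring rule, and no reading of that rule admits those values. Even in the harmless case the printed figures are wrong for the printed endpoint.

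**Conclusion.** The point holds as a scale mismatch. The means of 163.6 and 115.0 and the SD of 89.5 are impossible on a score bounded at 81 (or 90), with an SD bounded at about 40.5 (or 45). They belong to another scale or to an undivided sum, and the article does not say which. This conclusion rests only on the article's own scoring rule.

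The consequence for power is open. Under assumption A there is none. Under assumption B the roughly 85% power is unsupported for the severity score: over assumed SD/mean of 0.45 to 0.70, unadjusted power for a 30% reduction runs from 0.96 to 0.66 at 62 per arm and from 0.97 to 0.71 at 70. It should be corrected because these are the only figures given as the basis for N.

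**What to change.** State the instrument and scoring behind the cited means and SD. Restate the mean, the SD and the 30% difference in severity-score units. If the source reported undivided seven-day sums under the same item rule, say so and divide by 7 (23.4, 16.4, SD 12.8, difference 6.9).

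If the source used another instrument, restate the power that 70 per arm gives over a range of SD/mean on the severity score. The pre-randomisation diaries may inform that range, with three precautions:
- Pool them without reference to allocation.
- Use single-month scores. Follow-up is measured over one month, and averaging two months shrinks the SD.
- Treat the resulting SD/mean as a likely lower bound. Women are admitted for moderate-to-severe symptoms on the same diary, which raises the mean and truncates the spread, so power computed from it would tend to be too favourable.

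Keep N at 140. The work is one reworded paragraph and, if the diaries are used, one descriptive calculation on data collected before randomisation. The cost is that the stated power may become less favourable.
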